## Outcome measures and analysis

The primary outcomes are as follows: 1) safety via biomarkers of systemic inflammation (C-reactive protein), lipids (total cholesterol, high-density lipoprotein cholesterol, low-density lipoprotein cholesterol and triglycerides), sodium, liver enzymes (alanine aminotransferase, aspartate transaminase, alkaline phosphatase, albumin, bilirubin, total protein, nutritional ketosis (β-hydroxybutyrate) and glycemic status (fasting blood glucose and insulin)); 2) neurological recovery (AIS) motor and sensory scores and EPTs; 3) functional independence (SCIM); 4) microbiome composition; and 5) serum biomarkers (targeted proteomics).

In compliance with goals of the National Institute of Neurological Disorders and Stroke common data elements initiative, we are utilizing portions of the SCI common data elements that are expected to increase the efficiency and effectiveness of our clinical research study and diet intervention, increase data quality, and facilitate data sharing and comparisons across studies. For data analyses and results reporting, we adhere to the guidelines for reporting results using the international spinal cord core dataset [28].

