### Procedures to determine gut microbiome composition

Microbiome collection and analysis are performed using established protocols [18]. Briefly, stool samples are collected in ParaPak vials (Meridian Biosciences, Inc., Cincinnati, OH, USA) and consequently diluted to 0.1 mg/ml in Cary-Blair medium for a total volume of 20 ml with 10% glycerol (by volume). Aliquots of 5 ml are stored at −80°C in cryovial tubes until DNA extraction. Stool bacterial DNA is extracted using a Zymo Research Fecal DNA isolation kit (Zymo Research, Irvine, CA, USA) as per the manufacturer’s instructions. Polymerase chain reaction is then used to amplify the V4 region of the 16S rRNA gene. The polymerase chain reaction products are then retrieved after separation on an agarose gel using electrophoresis, excised from the gel, and subsequently purified with a QIAquick Gel Extraction Kit (Qiagen, Germantown, MD, USA). The Illumina MiSeq DNA sequencing platform is used to sequence 250 base paired-end kits.

Microbiome analyses will be performed using the Quantitative Insights into Microbial Ecology bioinformatics software and QWRAP program as previously described [18]. Briefly, quality assessment and filtering of low-quality data will be performed using the FASTQC and FASTX toolsets, respectively. A combination of tools within the Quantitative Insights into Microbial Ecology software suite will be utilized for clustering reads into operational taxonomy units (uclust), taxa assignment (RDP classifier using the Greengenes 16S rDNA database) and, as necessary, alignment and phylogenetic inference (using PyNAST and FastTree). These procedures will allow us to quantitatively assess the microbiome population down to the genus, if not species, level. For comparative analyses, indices of alpha (Chao1, Observed species, Phylogenetic distance, Simpson’s index and Shannon’s index) and beta diversity (Bray–Curtis dissimilarity, unweighted UniFrac and weighted UniFrac) will be computed [18].

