### Power calculations

Power calculations were performed using nQuery Advisor + nTerim 3.0, and assume a two-sided statistical test and a significance level of 5%. We obtained estimates of the standard deviation for the motor score of 23.5 and for the light touch score of 33 (both based on our preliminary data). With a final sample size of 24 participants per group, and also assuming a two-group *t* test and the prior assumptions, we have 80% power to detect between-group differences of 19.5 in the motor score and 27.3 in the light touch score as being statistically significant. With a final sample size of 24 participants per group, and assuming a paired *t* test and the prior assumptions, we have 80% power to detect within-group changes of 14.1 in the motor score and 19.8 in the light touch score as being statistically significant. All of these differences are approximately at the same levels as those that Kramer et al. detected as being statistically significant and clinically meaningful [36]. We believe that these estimates are conservative since we are performing our primary statistical analyses for between-group and within-group comparisons simultaneously using statistical methods that are more sophisticated than those that are assumed here. Given our history in SCI patient recruitment and the large SCI patient base at the UAB SRC, we fully expect to meet our recruitment goal.

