### Statistical analysis

Statistical analyses for neurological recovery will include comparisons of means of motor and sensory function, functional independence and serum measurements (e.g., glucose, insulin, alanine aminotransferase and aspartate transaminase) between the two groups, as well as comparisons within each group of the changes from baseline to rehabilitation to discharge (which should take approximately 5 weeks). Descriptive statistics, including measures of central tendency (sample mean, sample median) and dispersion (variance) will be calculated for each group. For safety outcomes, instead of comparing the two groups to the established standard safety values, we will compare circulating levels of proposed outcomes at the various time points among the two groups. If there are no significant group differences in these outcomes, we will conclude that the KD intervention is safe. We will also calculate 95% confidence intervals for the mean group differences for these outcomes as an additional check on safety and feasibility. The primary method of analysis will be analysis of covariance (ANCOVA), regressing the 5-week outcomes (safety, motor and sensory recovery, functional independence, and glycemic state) on the randomly assigned diet, baseline values of the measures, and other covariates such as age and sex. Repeated measures ANCOVA will also be used. Statistical assumptions will be assessed using box plots, residual plots and normal probability plots. Secondary analyses, accounting for all time points, will be conducted using mixed linear models, including repeated measures models. An appropriate structure for the covariance matrix (e.g., the unstructured covariance matrix) will be selected for these models using the final data. When a model term is statistically significant, the Tukey–Kramer multiple comparisons test will be used to determine which specific pair of means are significantly different. This method will allow us to compare changes over time (within-group changes) and differences between groups simultaneously. Covariates (e.g., length of enteral and solid feeding and length of stay in acute and rehabilitation care) will be accounted for in these analyses. Overall cross-sectional between-group comparisons, such as baseline comparisons used to examine pretest parameters, may be performed using the two-group *t* test, and overall within-group comparisons may be performed using the paired *t* test. If assumptions of normality of distribution for the above tests are not tenable, variables may be transformed prior to analysis, or appropriate nonparametric tests, such as the Wilcoxon rank-sum and signed-rank tests, may be used. Statistical tests will be two-sided and will be performed using a 5% significance level. Stratified analyses accounting for different injury levels will also be performed. These analyses will be specific to the distribution of data in each individual subgroup, which will minimize heterogeneity and allow us to analyze subgroups that may be more statistically homogenous and clinically relevant. SAS software, version 9.4 or later, will be used to conduct the statistical analyses. Multiple imputation methods will be used to address missing data for variables with moderate amounts of missing data (≥10%) and after examining whether data are missing completely at random, missing at random, or missing not at random. Missing data analysis will not be performed on variables with <10% missing data to avoid statistical bias larger than that obtained through the use of complete case analysis.

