
For microbiome analysis, alpha diversity indices will be analyzed using linear mixed-model with time (pre- and post-) and group (KD and SD) as fixed factors and participant as a random effect. Permutational multivariate analysis of variance testing will be used to assess the effects of time, treatment, and time × treatment on beta diversity indices. The principal coordinate analysis will be performed to visualize the beta diversity distance matrices [18].

For targeted proteomics, three specific analytic approaches will be utilized. First, two-sample *t* tests, or Wilcoxon rank-sum tests if the normality assumption is questionable, will be used to examine differences in the number of selected peptides and proteins between diet groups at discharge (approximately 5 weeks). Because of the number of proteins to be examined, a false discovery rate of 0.2 will be used to account for multiple hypothesis tests. The second approach will examine the manner in which levels of selected peptides vary across the longitudinal time points of baseline, rehabilitation and discharge. To examine these patterns, mixed linear models such as repeated measures models using time as a within-person factor and diet as a between-person factor will be constructed. Finally, Pearson’s correlation will be used to measure the strength and direction of linear associations between selected peptide levels and 5-week outcomes of safety, neurological, functional and glycemic status. 

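### The beta-diversity PERMANOVA names only time, treatment and time × treatment and does not say how each participant's paired pre and post samples are handled; under ordinary unrestricted permutation the treatment test would be too liberal and the other two too conservative

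*Protocol article*

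**What the plan says.** All references are to the protocol article.

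- Outcome measures and analysis lists "4) microbiome composition" among the primary outcomes.
- Procedures to determine gut microbiome composition names three distances: "beta diversity (Bray–Curtis dissimilarity, unweighted UniFrac and weighted UniFrac) will be computed".
- Statistical analysis, microbiome paragraph, gives alpha diversity a "linear mixed-model with time (pre- and post-) and group (KD and SD) as fixed factors and participant as a random effect".
- The next sentence covers beta diversity: "Permutational multivariate analysis of variance testing will be used to assess the effects of time, treatment, and time × treatment on beta diversity indices". It names no participant term, strata, blocking or permutation unit.
- The proteomics paragraph that follows specifies repeated-measures models in which time varies within the person and diet between persons.
- The general rule in the same section is: "Statistical tests will be two-sided and will be performed using a 5% significance level".
- The Abstract has stool collected at baseline and again after 5 weeks of diet. Power calculations assumes completers: "With a final sample size of 24 participants per group".

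**The concern.** Two stool samples from one person usually resemble each other more than samples from two people. An ordinary PERMANOVA with these three terms builds its reference distribution by shuffling samples over all positions. That treats a person's two samples as no more alike than any other two.

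The error then runs in opposite directions. Treatment varies only between people, so it would be judged against too small an error. Time and time × treatment vary within people, so they would be judged against too large an error. An inert diet could be reported as shifting the microbiome, while a real diet effect on change could be missed.

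The sentence also does not say which of its three terms is the diet effect.

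**Working it through.** **Inputs from the article.** 24 per group gives 2 × 24 = 48 participants (also 80% of 60). With a pre and a post sample each, that is 2 × 48 = 96 samples. The level is 5%, two-sided.

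**The plan's own figures.** The stated 80% power reproduces by the noncentral t distribution. Between groups it is 80.3% for motor (noncentrality 19.5 / (23.5 × √(2/24)) = 2.87) and 80.1% for light touch. Within groups it is 80.4% for both. None of these figures concerns the microbiome. The article gives no within-person correlation, effect size or power for beta diversity, so those below are assumptions.

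**Direction of the error.** Give each sample unit variance in each of p independent dimensions and let ρ be the correlation between a person's two samples. Code each contrast ±1 and scale it by 1/√96.

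- Treatment adds a person's two samples. Its variance per dimension is 48 × (2 + 2ρ)/96 = 1 + ρ.
- Time and time × treatment subtract them. Their variance is 48 × (2 − 2ρ)/96 = 1 − ρ.
- Unrestricted permutation refers all three to a variance of about 1.

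With c the 95th percentile of χ² on p degrees of freedom, the large-sample rejection rate under no effect is P(χ²ₚ > c/(1 + ρ)) for treatment and P(χ²ₚ > c/(1 − ρ)) for the other two. For example, with p = 1 and ρ = 0.5, c = 3.84 and 3.84/1.5 = 2.56, which gives 11.0%.

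| p | treatment, ρ = 0.3 / 0.5 / 0.7 | time × treatment, ρ = 0.3 / 0.5 / 0.7 |
|---|---|---|
| 1 | 8.6 / 11.0 / 13.3% | 1.9 / 0.6 / 0.04% |
| 5 | 13.0 / 19.4 / 26.0% | 0.7 / 0.05 / 0% |
| 20 | 23.5 / 40.1 / 55.6% | 0.1 / 0 / 0% |

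**Simulation with Bray–Curtis distances, no diet effect, unrestricted permutation** (24 per arm, ρ = 0.3 / 0.5 / 0.7):

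| set-up | treatment | time × treatment |
|---|---|---|
| 40 taxa | 16.9 / 31.6 / 41.1% | 0.6 / 0 / 0% |
| 60 taxa, first | 14 / 26 / 34% | 1.7 / 0 / 0% |
| 60 taxa, second | 10 / 22 / 30% | 1 / 0 / 0% |
| 100 taxa | 19 / 34 / 48% | 0.3 / 0 / 0% |

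In the 40-taxa set-up (800 runs, 199 permutations) the time term rejected in 0.75 / 0 / 0%. At ρ = 0 all three terms were near nominal (4.0–5.75%).

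**Power of time × treatment, unrestricted against restricted permutation.** In the 40-taxa set-up, 8 taxa shift by 0.4, 0.6 or 0.8 SD (300 runs):

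| ρ | small | medium | large |
|---|---|---|---|
| 0.3 | 14 vs 36% | 37 vs 69% | 82 vs 95% |
| 0.5 | 3 vs 48% | 27 vs 85% | 75 vs 98% |
| 0.7 | 0.3 vs 64% | 12 vs 96% | 63 vs 99.7% |

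Here the restricted test swaps pre and post within participants. That is valid in this set-up because its null has no common time trend. Its null rejection was 4.8 / 7.3 / 4.5%.

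Permuting diet labels between whole participants leaves a common time trend intact, so it is the scheme to prefer. With it, power against unrestricted permutation at ρ = 0.3 / 0.5 / 0.7 was:

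- 100 taxa (0.7 SD on 20 taxa): 41 / 57 / 83% against 8 / 1 / 0%.
- 60 taxa, first (0.7 SD on 12 taxa): 39 / 46 / 69% against 11 / 4 / 1%.
- 60 taxa, second: 28 / 47 / 79% against 6 / 8 / 1%.

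Its null rejection was 5.7–6.5% with 100 taxa and 4.3 / 6.3 / 5.3% in the first 60-taxa set-up. Monte Carlo standard errors for the 40-taxa runs are about 0.8 points at 5%, 1.6 at 30%, and up to 2.9 for power.

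**No single scheme serves all three terms.** Swapping samples only within participants leaves every sample's diet label, and so the treatment sum of squares, unchanged. It gives no treatment test. Permuting whole participants leaves the time labels unchanged and gives no time test.

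**Which term is the diet effect.** Suppose diet shifts post samples by d and, by randomisation, pre samples by 0. The treatment main effect averages these to (0 + d)/2 = d/2 and carries the larger variance 1 + ρ. Time × treatment compares changes, d − 0 = d, and carries 1 − ρ. In the 40-taxa set-up at ρ = 0.7, treatment tested correctly by whole-participant permutation had power of 15 / 45 / 65%, against 64 / 96 / 99.7% for time × treatment.

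**The case against.** The strongest reply is that the article never says samples are permuted freely. A reader might infer from the three listed terms that the plan treats all 96 samples as exchangeable and so uses an invalid test. The text does not support that. It is silent on the scheme, restricted permutation is compatible with it, and it cites an earlier publication, not available here, for its microbiome methods. The neighbouring models show that the authors know the samples are paired, and an unseen analysis plan may settle the matter. This stands, and the point must stay conditional.

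It does not dispose of the point. The same paragraph does name the person for alpha diversity, "group (KD and SD) as fixed factors and participant as a random effect", so dependence is specified at this level of detail and then drops out for beta diversity. Nor can one unstated restriction rescue the sentence, because the three effects it promises need different permutation units.

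A second reply is that the size depends on assumptions. That also stands. A reader might infer that time × treatment loses most of its power whatever the effect. The results do not bear that out: for a large effect at ρ = 0.3 the comparison is 82% with 95%. At ρ = 0 there is no problem, and the article gives nothing from which to judge the correlation between a sample taken within 72 h of injury and one about 5 weeks later.

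A third reply is that little hangs on this test. The microbiome is absent from the Abstract's primary goals, from the outcomes named for the primary ANCOVA and from the power section. That limits the consequence, but the outcomes section still lists microbiome composition as primary.

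**Conclusion.** The concern holds in conditional form. As written, the beta-diversity sentence does not account for two samples per participant, unlike the models beside it, and does not identify the term that carries the diet effect.

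If the three-term model is run with unrestricted permutation and samples within a person are positively correlated, the treatment term is anti-conservative. Under no effect it rejects in about 10–48% of simulated trials at correlations of 0.3–0.7; the large-sample approximation spans 8.6–55.6% across 1 to 20 dimensions. Time and time × treatment are conservative, with rejection of at most about 2% under no effect. The power lost for time × treatment is severe for small to moderate effects, above all at correlations of 0.5 or more, and smaller for large ones.

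The directions follow from the design and a positive correlation. The percentages rest on assumed correlations, numbers of taxa and effect sizes, and only Bray–Curtis was simulated. The documents do not show that the sponsor intends unrestricted permutation.

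**What to change.** Replace the sentence with wording to this effect:

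> The diet effect on beta diversity is the time × treatment term of the PERMANOVA. Its null distribution is obtained by permuting diet labels between whole participants, keeping each participant's pre and post samples together. The time effect is tested by permuting pre and post within participants. The treatment main effect is not used as evidence of a diet effect.

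The last clause is needed for two reasons. The main effect averages in samples taken before the diet. And if participant is added as a model term, treatment is constant within participant and is aliased with it. Permuting diet labels between participants matches the individual 1:1 randomisation and leaves any common time trend intact.

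The cost is a short amendment before analysis, a little extra analysis work and no new data. The one practical condition is software that supports restricted permutation. The article names tools for the microbiome work and SAS for the statistics in general, but none specifically for the PERMANOVA, so the chosen tool should be checked.

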**Fig. 2 Fig2:**
[figure not shown]
Standard Protocol Items: Recommendations for Interventional Trials (SPIRIT) schedule. *Allocation and baseline testing occur within 72 h of injury; postintervention assessments are performed prior to each patient’s discharge. ^¥^Including cholesterol, triglycerides, high-density lipoprotein cholesterol and calculated low-density lipoprotein cholesterol. ^&^As reflected by liver enzymes, alanine aminotransferase, aspartate transaminase, alkaline phosphatase, albumin, bilirubin and total protein. ^$^Serum fibrinogen, extracellular signal-regulated kinase 1/2, CD11b/CD18 integrin receptor, epidermal growth factor and receptor levels. AIS American Spinal Injury Association Impairment Scale, Wk week

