#### Targeted protein analysis

Peptides representing fibrinogen, extracellular signal-regulated kinase 1/2, CD11b/CD18 integrin receptor and epidermal growth factor are selected from either preliminary data (fibrinogen) or using Skyline, a targeted proteomics software tool [33]. Predicted product ions from each peptide are used to set up a multiple reaction monitoring liquid chromatography tandem MS (LC-MS/MS) assay carried out on a SCIEX 6500 Qtrap using microflow LC. This instrument is very sensitive and is capable of detecting peptides in the amol range. The tryptic peptides are resolved on a 5–50% linear gradient of acetonitrile in 0.1% formic acid mobile phase before entering the electrospray ionization (ESI) interface of the mass spectrometer. Synthetic peptides will be used to obtain quantitative data. To obtain absolute quantitative data on the selected peptide(s), ^13^C/^15^N-isotopically labeled versions of the peptide(s) will be prepared [34].

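### The first targeted-proteomics comparison between diets names the number of pre-selected peptides and proteins as its variable, where it should name the level of each

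*Protocol article*

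**What the plan says.** The Outcome measures and analysis section of the protocol article lists serum biomarkers by targeted proteomics as the fifth primary outcome. The Statistical analysis section then gives three approaches to it.

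- **First approach.** The tests are "First, two-sample *t* tests, or Wilcoxon rank-sum tests if the normality assumption is questionable", and they "will be used to examine differences in the number of selected peptides and proteins between diet groups at discharge (approximately 5 weeks"). The multiplicity rule follows at once: "Because of the number of proteins to be examined, a false discovery rate of 0.2 will be used to account for multiple hypothesis tests".
- **Second approach.** "The second approach will examine the manner in which levels of selected peptides vary across the longitudinal time points of baseline, rehabilitation and discharge". For this, "repeated measures models using time as a within-person factor and diet as a between-person factor will be constructed".
- **Third approach.** Pearson correlation of peptide levels with the 5-week outcomes.

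The Targeted protein analysis section describes the panel: "Peptides representing fibrinogen, extracellular signal-regulated kinase 1/2, CD11b/CD18 integrin receptor and epidermal growth factor are selected", either from preliminary data or with a targeted-proteomics software tool. The same section plans isotopically labelled peptides "To obtain absolute quantitative data on the selected peptide(s"). The Fig. 2 legend lists the serum markers as "Serum fibrinogen, extracellular signal-regulated kinase 1/2, CD11b/CD18 integrin receptor, epidermal growth factor and receptor levels".

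**The concern.** The first approach is the only one of the three framed as a two-group test at discharge, and the only one to which the false discovery rate is attached. The variable it names is a count. In a targeted assay, how many peptides are selected is settled before any participant's serum is analysed, so that count carries no information about diet.

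The biological question is about amounts. The Discussion section rests the proteomic hypothesis on fibrinogen being present at lower levels in the ketogenic-diet samples of the pilot study. An analyst who followed the sentence literally would run a test that cannot bear on that hypothesis. One who departed from it would be changing the stated analysis of a listed primary outcome without written support.

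**Working it through.** The document states no sample size or power for proteomics, so there is no figure to reproduce. The check compares the stated variable with the rest of the plan.

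**1. Is the variable a participant outcome?** The Targeted protein analysis section has the peptides chosen from preliminary data or by software. Selection therefore happens once, for the assay. If *c* peptides are selected, every participant in both groups has the value *c*.

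**2. What does the stated test do with a constant?** The Power calculations section assumes 24 participants per group. The t statistic is

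t = (mean₁ − mean₂) / (s·√(1/24 + 1/24)).

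With every value equal to *c*, mean₁ − mean₂ = *c* − *c* = 0 and s = 0, so t = 0/0, which is undefined. Running it with *c* = 4 in 24 against 24 participants returned no t statistic and no p value. The rank-sum test, with all 48 values tied, returned p = 1.0. The choice of *c* is immaterial. This illustrates the logic and is not an estimate of anything in the trial.

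**3. Does the variable fit the multiplicity rule?** A count summed over the panel gives one number per participant. At most, that yields one test for peptides and one for proteins. A false discovery rate justified by how many proteins are examined needs one p value per protein. The rule fits tests on the level of each protein and does not fit a test on a count.

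**4. Does the variable fit the assay?** The labelled standards deliver an absolute quantity for each selected peptide. A count uses none of that information.

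**5. Does it fit the neighbouring analyses?** The second and third approaches both take peptide levels as their variable. Only the first takes a number.

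**6. Is the family of tests fixed?** Counting entries as listed, the Targeted protein analysis section has four: fibrinogen, extracellular signal-regulated kinase 1/2, the CD11b/CD18 integrin receptor and epidermal growth factor. The Fig. 2 legend adds a receptor after epidermal growth factor, read here as the epidermal growth factor receptor, which makes five. The procedure for controlling the false discovery rate is not named. If it is Benjamini–Hochberg (an assumption), the threshold for the smallest p value is 0.2/4 = 0.05 with four tests and 0.2/5 = 0.04 with five. The list therefore affects the decision rule.

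**The case against.** The strongest reply is that this is a drafting slip whose meaning is clear from context. The tests are in the plural, the next sentence speaks of multiple hypothesis tests because of the number of proteins, and the assay is built to quantify. No sensible analyst would test a constant. The SWATH-MS analysis section also uses peak areas for protein quantification, which shows that the proteomics plan rests on amounts. This stands as an account of what was most likely intended, and it keeps the point small. It does not make the stated variable right. A full analysis plan may supply detail that an article omits, but here the article states a variable, and it is the wrong one.

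A reader might go further and infer that the plan has no analysis able to show a diet effect on protein levels. The documents do not support that. The second approach models levels at baseline, rehabilitation and discharge with diet as a between-person factor, and it is untouched by the wording of the first.

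A reader might also take *number* to mean the number detected, and attach a power loss to it. A detected count could vary between participants, and the documents do not rule that reading out. They give no detection rate, however, and the answer depends almost wholly on that assumption. Take four independent proteins, each 0.83 SD lower on the ketogenic diet, with 24 per group. Simulated rejection by a count test was 0% if every value is detected, 55% if 1% of control values fall below the detection limit, and 92% if 5% do. If detection is instead assumed to be unrelated to level, the test has no power by construction. No single figure can be defended.

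**Conclusion.** The point holds in a limited form. The first targeted-proteomics comparison names a variable that the pre-selected panel fixes in advance. Taken literally, the test cannot show a difference in protein levels, and it conflicts with its own false discovery rule and with the quantitative assay.

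The conclusion rests on reading *selected* as the Targeted protein analysis section uses it, namely as a choice made for the assay. It extends to that one comparison only. The longitudinal model of levels by diet and the correlation analysis stand as written. No loss of power is claimed.

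The mismatch in the protein list is a secondary point. It matters because it leaves the number of tests under the false discovery rate open. The correction is small, but it concerns a listed primary outcome and should be made before the proteomic data are analysed.

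**What to change.** - In the targeted-proteomics paragraph of the Statistical analysis section, change the variable of the first approach from *the number of* to *the level of each* selected peptide or protein. State that there is one test per protein and that the 0.2 false discovery rate applies across those tests.
- Make the protein list the same in the Fig. 2 legend and the Targeted protein analysis section, saying whether the epidermal growth factor receptor is included, so that the family of tests is fixed.

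The cost is a sentence of wording and one reconciled list. No new samples or assays are needed, because absolute quantification of the selected peptides is already planned.

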## Abstract

**Background:**

Therapies that significantly improve the neurological and functional recovery of individuals with spinal cord injury (SCI) are still urgently needed. The ketogenic diet (KD) has been shown to improve forelimb motor function in an SCI rat model, likely by reducing inflammation and cell death in the spinal cord. Furthermore, our recent pilot study in patients with SCI showed that, compared with a standard hospital diet (SD), 5 weeks of KD started during acute care improved upper extremity motor function and reduced serum levels of a neuroinflammatory blood protein. The primary goals of the current study are to: 1) show the safety and feasibility of administering a KD during acute care for SCI; 2) determine if consuming 5 weeks of a KD significantly improves motor and sensory functions, functional independence and glycemic control; and 3) quantify serum biomarkers that are linked to improvements in neurological recovery and functional independence via targeted proteomics.

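### The proteomics false discovery rate is stated only for the discharge comparison; the peptide-by-outcome correlations that serve the biomarker aim have just the general 5% level

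*Protocol article*

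**What the plan says.** The third goal in the Abstract, repeated at the end of the Background, is to "quantify serum biomarkers that are linked to improvements in neurological recovery and functional independence via targeted proteomics". Outcome measures and analysis lists serum biomarkers as the fifth primary outcome.

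For targeted proteomics, the Statistical analysis section announces three approaches.

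- **First:** two-sample t or Wilcoxon rank-sum tests that "examine differences in the number of selected peptides and proteins between diet groups at discharge (approximately 5 weeks"). The multiplicity sentence follows at once: "Because of the number of proteins to be examined, a false discovery rate of 0.2 will be used to account for multiple hypothesis tests".
- **Second:** mixed linear models of peptide levels over baseline, rehabilitation and discharge, by diet.
- **Third:** "Pearson’s correlation will be used to measure the strength and direction of linear associations between selected peptide levels and 5-week outcomes of safety, neurological, functional", with glycemic status added to the list.

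No multiplicity statement accompanies the second or third approach. The rule stated earlier in the section for all analyses is: "Statistical tests will be two-sided and will be performed using a 5% significance level".

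**The concern.** The first approach asks whether peptides differ by diet, and the second asks how they change over time. Only the third sets peptides against neurological and functional outcomes, so of the three it alone speaks to the third goal. The stated FDR therefore sits on a family that does not test that goal, and the family that does is left at 5% per test.

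The uncontrolled family is also the larger one. The discharge comparison needs one test per peptide or protein. The correlations multiply the same peptides by every 5-week outcome. The reason given for controlling the first family, the number of tests, applies with more force to the third.

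At stake is a false report that a protein is associated with recovery, under a goal that the article places among its primary ones.

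**Working it through.** The article states no number of correlations and no expected number of false positives, so there is no figure of its own to reproduce. The counts below are assumptions built from its lists.

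**Inputs**

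- Proteins: 4, from Targeted protein analysis ("Peptides representing fibrinogen, extracellular signal-regulated kinase 1/2, CD11b/CD18 integrin receptor and epidermal growth factor are selected"). The Fig. 2 legend gives 5, because it adds the growth factor receptor ("Serum fibrinogen, extracellular signal-regulated kinase 1/2, CD11b/CD18 integrin receptor, epidermal growth factor and receptor levels"). Peptides per protein are not stated; one value per protein is assumed.
- Outcomes within the third goal: 5, from Outcome measures and analysis, counted as motor, light touch, pin-prick, electrical perception threshold (EPT) and the Spinal Cord Independence Measure (SCIM). Splitting motor into upper and lower extremity gives 6.
- Safety and glycemic outcomes: 15. Six come from "safety via biomarkers of systemic inflammation (C-reactive protein), lipids (total cholesterol, high-density lipoprotein cholesterol, low-density lipoprotein cholesterol and triglycerides), sodium, liver enzymes" (C-reactive protein, four lipids, sodium). Nine follow in the same sentence (six liver markers, β-hydroxybutyrate, glucose, insulin).
- Completers: 48 (Abstract, Methods/design). Level: two-sided 5%.

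**Nominal threshold.** With n = 48 there are 46 degrees of freedom and t = 2.013, so |r| = t/√(46 + t²) = 2.013/√50.05 ≈ 0.285.

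**Expected chance findings.** This is pairs × 0.05 with no true association, whatever the dependence between tests.

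- 4 × 5 = 20 pairs: 20 × 0.05 = 1.0.
- 5 × 6 = 30 pairs: 30 × 0.05 = 1.5.
- For comparison, the discharge family on the same 4 proteins: 4 × 0.05 = 0.2.

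**Chance of at least one, 20 pairs.**

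- Independent tests: 1 − 0.95²⁰ = 0.64.
- Correlated: a simulation of 4,000 null datasets of 48 participants, with correlation 0.5 among outcomes and 0.3 among proteins, gives 0.53. Those two correlations are assumptions.

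**Proteins flagged, 20 pairs.** The expected number of the 4 proteins with at least one chance hit is 4 × (1 − 0.95⁵) = 0.90 if independent, and 0.73 in the correlated simulation.

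**With Benjamini–Hochberg at 0.2 over the 20 pairs.** The simulated chance of any false finding is 0.197 if independent and 0.175 if correlated. This agrees with theory: when no association is real, the FDR equals the chance of any false finding, which is held at or below 0.2.

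**The case against.** Three objections deserve an answer.

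*The placement may be incidental, and the analysis plan may settle it.* The reason given for the FDR is general enough to cover all three approaches, and multiplicity detail is often left to an analysis plan, which is not shown here. This stands as a caution: the article does not say that the correlations go uncontrolled. But it does state a multiplicity rule and places it inside one of three enumerated analyses. The point concerns where that stated rule sits, not a detail left out.

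*Correlation is described as estimation.* The article speaks of measuring strength and direction, and nowhere says that p < 0.05 makes a biomarker linked. That stands, so it would be wrong to say that any |r| above 0.285 meets the third goal. However, the correlations are not labelled exploratory, and any p-value attached to them falls under the general 5% level.

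*The size is easily overstated.* A reader might cross all 4 proteins with all 20 outcomes (15 + 5), obtain 80 pairs and 80 × 0.05 = 4 chance findings, and infer that about four linked biomarkers will arise by chance. The documents do not support this:

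- 80 is an assumed count; other protein counts give up to 7 × 20 = 140.
- 60 of the 80 pairs (4 × 15) involve safety or glycemic markers, which are outside the third goal.
- Four significant correlations are not four biomarkers. Over 80 pairs the expected number of proteins with any chance hit is about 2.6 of 4 if independent, and 1.7 to 2.2 in correlated simulations.
- Independence cannot hold throughout that grid, since low-density lipoprotein cholesterol is calculated by the Friedewald formula.
- Four is an average when no association is real, not a prediction.

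**Conclusion.** The point holds on the narrower count. As written, the FDR of 0.2 belongs to the discharge comparison, and no control beyond the general 5% level is stated for the correlations that serve the third goal. On the 20 pairs relevant to that goal, a trial with no true association would still be more likely than not to show at least one nominally significant correlation (64% independent, about 53% correlated), with 1.0 expected, or 1.5 on 30 pairs.

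These figures assume one value per protein, 48 completers, and each correlation being tested at 5%. Several peptides per protein would enlarge the family, and stronger dependence would lower the chance of at least one finding without changing the expected number. The matter should be corrected before analysis; it does not affect the design or conduct of the trial.

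**What to change.** In the targeted-proteomics paragraph of Statistical analysis:

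- Define the pairs formed by the targeted proteins and the neurological and functional outcomes (motor, light touch, pin-prick, EPT, SCIM) as one family. EPT belongs in it because the article lists it under neurological recovery.
- Apply Benjamini–Hochberg control across that family at the article's own FDR of 0.2. Nothing in the document argues for a different rate here.
- Report correlations with safety and glycemic markers as descriptive, with 95% confidence intervals and no claims of significance.

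The cost is a change of wording and adjusted p-values; no data, visits or participants are added. Fewer correlations will generally be declared. With 20 pairs, a lone finding needs p ≤ 0.2/20 = 0.01, and the cut-off rises by 0.01 for each further pair that passes. It exceeds 0.05 only once six or more pass (6 × 0.01 = 0.06), so the text should also say whether the 5% level must be met as well.
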